### Psychological Responses

After each set of each exercise, participants will be asked to rate their perceived exertion using the OMNI-Resistance Exercise scale from 0 to 10 [38]. During each session, participants will be asked to rank their feeling (before and immediately after) [43], enjoyment (immediately after) [44], self-efficacy (immediately after) [45], discomfort (5 min after the resistance exercise sessions) [46], and session rating of perceived exertion (5 min after the resistance exercise sessions) [29] using validated scales.

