**Figure 1 figure1:**
[figure not shown]
SPIRIT (Standard Protocol Items: Recommendations for Interventional Trial) schedule of assessments at different time points. a: Sessions order is randomized with at least a 4-day washout period.

During experimental sessions, participants’ diets will be strictly controlled, and all food and drink will be provided to the participants. Glycemic control will be monitored using a CGM device throughout the experimental sessions. The exercise sessions will be matched for total volume load and session density, but proximity to concentric muscular failure (ie, incapacity to continue the set in the concentric phase of the movement) will be manipulated to vary the effort between the exercise sessions. The control session will follow identical procedures except that participants will remain sedentary for the same period of time they are to exercise in the exercise sessions.

Participants will be asked to refrain from moderate- to high-intensity physical exertion for 72 hours before the experimental sessions. The evening before the exercise or control sessions (day 1), at ~5 PM, participants will report to the laboratory to be instrumented with the CGM device and an accelerometer (to assess physical activity levels, refer to *Continuous Glucose Monitoring* subsection) and will receive dinner to be ingested at 6:30 PM and a snack to be ingested at 9:30 PM. The next morning (day 2), they will report fasted to the laboratory at 8:00 AM and ingest the provided breakfast at 8:30 AM. The exercise or control sessions will begin at 9:30 AM and will last ~50 minutes. They will perform 1 of 3 random sessions: a high-effort resistance exercise, a low-effort resistance exercise, or control session. After each session, psychological responses (perceived exertion, enjoyment, affect, discomfort, and self-efficacy) will be assessed.

After the session, participants will then be free to resume their daily activities after being given individualized meal bags and will be asked to consume lunch at 12:00 PM, a snack at 3:30 PM, dinner at 6:30 PM, and another snack at 9:30 PM, and in the following day (day 3), they will have breakfast at 8:30 AM, lunch at 12:00 PM, and a snack at 3:30 PM. After that, they will report to the laboratory between 5 and 6 PM to have the CGM device and accelerometer removed. Participants will be instructed to refrain from moderate- to high-intensity physical exertion until they are deinstrumented.

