### Diet and Physical Activity Levels

During the ~48-hour experimental situations, diet prescription will follow American Diabetes Association recommendations [49,50] to ensure a personalized diet based on their estimated energy requirements. Meals and snacks will be provided in individualized, pre-weighted packages and will be composed of ~55% carbohydrate, ~15% protein, and ~30% fat. The timing of ingestion will be strictly controlled to ensure a standardized diet. Diet prescription will be done by a registered dietitian nutritionist. The diet will be designed to meet the energy requirements as calculated with the Cunningham equation [51] multiplied by a physical activity level of 1.2 [11].

Participants will be instructed to maintain their habitual physical activity levels, and to not perform moderate- to high-intensity physical activity 72 hours before and during the experimental sessions. Physical activity levels will be assessed using a commercially available accelerometer (GT3X, ActiGraph).

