The statistical analysis will follow the principles of intention-to-treat analysis [57]. Thus, data from participants will be assessed as randomized, regardless of whether they received the randomized treatment, meaning that even if they fail to follow the physical activity and diet instructions, or fail to complete the sessions as required, their data will be included in the analyses. Furthermore, we will also analyze the data “per protocol” [58], meaning that participants who deviate from instructions will be excluded from the final analyses. Differences in results stemming from intention-to-treat and per-protocol analyses will be discussed accordingly. The available variables will also be compared between participants who withdraw from the study and those who complete the study.

The effect of resistance exercise on glycemic control will be calculated as the absolute and percentage change between control and resistance exercise situations. Data will be expressed as mean and SD, with a 95% CI. For the analysis of data normality, we will perform the Shapiro-Wilk test. For normally distributed data, ANOVA will be used with 1 source of variation (experimental condition). If a significant main effect is observed, the post hoc Tukey test will be conducted. For nonnormal data, the Kruskal-Wallis test or Friedman test will be used as appropriate. The effect size will be calculated and interpreted as follows: <0.2=no effect, 0.2-0.49=low effect, 0.5-0.79=medium effect, and >0.8=large effect [59,60]. The significance level is set at 5%. The Prism program (version 10.1.1, GraphPad Software) will be used to generate graphs and analyze results. This trial will be reported following the CONSORT (Consolidated Standards of Reporting Trials) guidelines [61-63].

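### Session baselines for feeling and glucose are recorded but have no term in the condition-only ANOVA, and pre-session glucose is mixed into the outcome; using them properly is cheap and likely, but not certain, to gain precision

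*Protocol article*

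**What the plan says.** **Feeling.** The Psychological Responses section states that "participants will be asked to rank their feeling (before and immediately after" the session. The other session-level scales are taken only afterwards: "enjoyment (immediately after) [44], self-efficacy (immediately after) [45], discomfort (5 min after the resistance exercise sessions", and session exertion likewise.

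**Glucose.** In Study Type and Design, on day 1 "at ~5 PM, participants will report to the laboratory to be instrumented with the CGM device and an accelerometer", and they "will receive dinner to be ingested at 6:30 PM and a snack to be ingested at 9:30 PM". Breakfast follows on day 2 at 8:30 AM, and then "The exercise or control sessions will begin at 9:30 AM and will last ~50 minutes". The sensor comes off between 5 and 6 PM on day 3. Food is supplied in weighed packages, and "The timing of ingestion will be strictly controlled to ensure a standardized diet" (Diet and Physical Activity Levels). For the third session, "The control session will follow identical procedures except that participants will remain sedentary".

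**Analysis.** The Statistical Analysis section specifies that, for normally distributed data, "ANOVA will be used with 1 source of variation (experimental condition"). It expresses the glycemic effect as the difference between the control and exercise sessions. The CGM Assessment section reports glucose over the full 48 hours, over each 24-hour half and over four clock periods. It makes no cut at the start of the session.

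**The concern.** In a crossover, stable differences between people drop out of the condition comparison. What remains as error is a person's variation from one session to the next. A value taken in the same session before the intervention may capture part of that variation, and this trial records such a value for feeling and for glucose. A model with condition as its only factor cannot use it as a covariate.

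For glucose there is a second cost. Hours before 9:30 AM on day 2 cannot show an exercise effect, yet they are averaged into the outcome, which shrinks any real difference.

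Precision matters here because the article's hypothesis is that effort does not affect glycemic control. A finding of no difference is informative only if the high-versus-low interval is narrow, and about 15 completers are planned.

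**Working it through.** **1. The plan's own figure.** The article gives no figure for baseline adjustment. Its sample size statement is 15 participants, power 0.96, from f = 0.2, alpha 0.05, target power 0.95, correlation 0.7 and nonsphericity 0.5. The numbers of groups and measurements are not given, so 15 does not follow from these inputs alone. If one assumes 3 groups and 48 hourly measurements in a within-between interaction, the result is N = 15 with power 0.956. For one group under three conditions, λ = f²·N·m·ε/(1 − ρ) = 0.04 × 15 × 3 × 0.5/0.3 = 3.0, and power at N = 15 is 0.36 (λ = 6.0 and power 0.54 at ε = 1). I use this only to take n = 15 as the number of completers and to show that precision is scarce.

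**2. Pre-session share of the glucose windows.** 5 PM to 9:30 AM is 16.5 h.

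- Full 48 h: 16.5/48 = 34% precedes the session.
- First 24 h, if counted from sensor fitting: 16.5/24 = 69% precedes it. A constant effect after session start would appear at (24 − 16.5)/24 = 31% of its size.
- Day 2 morning period (6 AM to 12 PM): 3.5/6 = 58% precedes it.

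The article does not state where the 24-hour periods begin. From session start to sensor removal only 31.5 to 32.5 h remain, too few for two full 24-hour periods, so counting from sensor fitting is the reading that fits best.

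**3. Effect of adjusting for the session baseline.** Let r be the within-participant, session-specific correlation of baseline and outcome. It is not in the article, so a range is assumed. With participant and condition in the model, residual df are d = 2(n − 1) = 28. The variance of a condition contrast, adjusted over unadjusted, is

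(1 − r²)(d − 1)/(d − 2) = (1 − r²) × 27/26.

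A change score has ratio 2(1 − r), assuming equal variances before and after.

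| r | Covariate: variance ratio | CI width ratio | Equivalent n (15/ratio) | Change score: variance ratio |
|---|---|---|---|---|
| 0 | 1.04 | 1.02 | 14.4 | 2.0 |
| 0.2 | 1.00 | 1.00 | 15.0 | 1.6 |
| 0.3 | 0.95 | 0.97 | 15.9 | 1.4 |
| 0.5 | 0.78 | 0.88 | 19.3 | 1.0 |
| 0.7 | 0.53 | 0.73 | 28.3 | 0.6 |

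Simulation (4,000 trials per value of r) gave 1.03, 1.00, 0.96, 0.78 and 0.53 for the covariate column. Break-even is where 1 − r² = 26/27, so r = √(1/27) = 0.19.

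Fitting period as well takes two more df. With d = 26 the multiplier is 25/24 = 1.042 instead of 27/26 = 1.038, a negligible change.

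**4. High-versus-low interval for glucose.** If the planning correlation of 0.7 applies, the unadjusted 95% half-width for this one comparison is 2.048 × √(2 × 0.3/15) = 0.41 SD. Multiplying by the CI width ratios gives about 0.40, 0.36 and 0.30 SD at r = 0.3, 0.5 and 0.7.

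**The case against.** **Covariate choice usually belongs in the SAP, and a condition-only ANOVA in a randomized crossover is valid.** The validity point stands. Randomized order balances session baselines in expectation, so leaving them out causes no bias. But the article is not silent: it fixes a one-factor model and glucose windows that ignore session start. Both can be improved with data already being collected.

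**A reader might infer that the plan gives away free precision.** The documents do not support that. The participant term already removes stable differences, and r is unknown. If the correlation of 0.7 held equally between all pairs of measurements, before and after included, r would be 0 and adjustment would cost about 4% in variance. The supplied meals, the limits on exertion and the instruction to keep medication unchanged may also lower r. On the other side, the article itself names menstrual phase as a possible confounder, and that would act on the hours before and after a session alike.

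**A reader might infer that the pre-session feeling score is excluded.** It is not. The text fixes the factor but not the dependent variable, so a one-factor ANOVA on the before-to-after change would fit. The use of the score is unspecified, and the change score is the weaker choice unless r exceeds 0.5.

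**Other limits.** Identical menus across sessions are a fair inference; the article says only that the diet is standardized. The 0.41 SD half-width rests on a correlation chosen for glucose and should not be carried over to feeling. Finally, the session sequence is revealed before the sessions begin, so anticipation could shift the pre-session feeling score.

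**Conclusion.** The point holds as a worthwhile improvement, not as an error that biases the trial.

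- The firmer part concerns the glucose windows. Pre-session hours make up 34% of the 48-hour outcome, and 69% of the first 24 hours if these run from sensor fitting. Removing them helps whatever r is.
- The precision part is conditional. At n = 15 the covariate costs about 4% of variance at r = 0, breaks even near r = 0.19, and saves about 5%, 22% and 47% at r = 0.3, 0.5 and 0.7. The possible loss is small beside the possible gain, but no value of r can be taken from the article.
- The scope is feeling and glucose only.

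These figures assume 15 completers with all three sessions and a linear relation between baseline and outcome.

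**What to change.** 1. Define the glucose outcomes from session start (9:30 AM, day 2). A full 24-hour average from that point is available within the 31.5 h that remain. The 48-hour and two-halves summaries can stay as descriptive reports, with their starting point stated.
2. Analyse post-session glucose and post-session feeling in a within-participant model with participant, period and condition. Add the session baseline as a prespecified covariate: mean glucose from sensor start to 9:30 AM on day 2, and the pre-session feeling score. Enter each as the participant's mean baseline plus the session's deviation from it. Do not use change scores.
3. Report the unadjusted comparison alongside, and tabulate the baselines by condition, chiefly to check feeling for anticipation.
4. Leave enjoyment, self-efficacy, discomfort and session exertion without a baseline term.
5. Reconcile the model named for the sample size (repeated measures with an interaction) with the one-factor model named for the analysis.

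Cost: analysis wording settled before allocation is revealed, and no new data. The baseline slope takes about one degree of freedom and period two. The team should confirm that the named software can fit this model.

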### Randomization and Blinding

After the fifth familiarization session, random allocation of the order of the experimental sessions’ participants will carry out will be performed as previously described [24-26]. The order in which the experimental sessions will be held will be randomized with the aid of the website. A collaborator not directly involved in any phase of the research (conceptualization, data collection and analysis, and reporting) will print the random orders generated by the program, insert them inside opaque, sequentially numbered envelopes, and seal them. After completing the fifth familiarization day, the envelope will be opened, and the sequence of experimental sessions will be revealed.

Due to characteristics inherent to this trial (resistance exercise), blinding of participants and researchers to exercise or control situations is not possible. However, participants and researchers will be blinded to CGM results (the blind model will be used). Furthermore, data and statistical analysis will be performed by a statistician blinded to groups and participants’ identities, as previously described [24-26].

### Exercise and Control Sessions

Participants will perform 2 exercise sessions and a control session, and the exercise sessions will be composed of 7 exercises (described above), both with the loads corresponding to 10-RM.

One of the exercise sessions will be a high-effort session (*high*), when participants will perform 3 sets per exercise (total of 21 sets) aiming at 8 repetitions per set. We anticipate participants will perform each repetition with a total duration of ~2.5 seconds. The resting period between exercises and sets will be 120 seconds. This will lead to a total session time of ~50 minutes.

The other session will be a low-effort one (*low*), when participants will perform 6 sets per exercise (total of 42 sets) but perform half of the number of repetitions of the *high* session (ie, 4 repetitions). A repetition duration of ~2.5 seconds and a resting period between exercises and sets of 60 seconds will also lead to a total session time of ~50 minutes.

Both the *high* and *low* sessions will have similar total volume-load and session density but differ in perceived effort after each set [47]. Pilot data from our laboratory in healthy untrained participants show that participants were able to complete both *high* and *low* sessions as prescribed, but average OMNI score after sets (8.5 vs 5.9), session rating of perceived exertion (7.5 vs 4), and perceived session discomfort (73 vs 40) were all higher in response to *high* sessions compared with *low* sessions.

For the control session, all procedures will be identical to the *high* session, with the exception of performing the resistance exercises. However, to simulate all other procedures participants will be positioned on the equipment for ~20 seconds for each of the 3 sets in each of the 7 exercises, but will not perform any repetitions, thus, performing sham sets.

### Heart Rate Assessment

To estimate cardiac work, heart rate will be assessed throughout the experimental sessions. Participants will be instrumented with a heart rate strap (Polar H10) and monitor (Polar V800), and their heart rate will be recorded continuously during the experimental situations. Data will be synced into Polar Flow and downloaded to a spreadsheet before being analyzed.

### CGM Assessment

Glycemic control will be assessed by a CGM device (Dexcom G6 Pro; Dexcom) every 5 minutes, over the ~48-hour experimental sessions. Reporting of variables will follow the most recent international guidelines consensus for clinical trials [48] and will include (1) time in range: 70-180 mg/dL; (2) time in tight range: 70-140 mg/dL; (3) time below range: <70 mg/dL; (4) time in level 1 hypoglycemia: 54-69 mg/dL; (5) time in level 2 hypoglycemia: <54 mg/dL; (6) time above range: >180 mg/dL; (7) time in level 1 hyperglycemia: 181-250 mg/dL; and (8) time in level 2 hyperglycemia: >250 mg/dL. Data will be reported as a percentage of time per day and as estimated hours and minutes per day. We will also report (9) average glucose concentration and (10) area under the curve, (11) glucose management indicator (used to predict long-term glucose exposure); (12) glycemia risk index (summary of the quality of glycemia), (13) glucose coefficient of variation; and (14) mean SD glucose (both are measures of dynamic glucose variability). Variables will be reported for the entire 48-hour collection period, for the first and second 24-hour periods, and stratified over 4 different periods: morning (6 AM to 12 PM), afternoon (12 PM to 6 PM), evening (6 PM to 12 AM), and nocturnal (12 AM to 6 AM) [11]. Individual data will be analyzed only if the percentage of data obtained is >70% of the anticipated amount of data collected during the collection period [48].

### Diet and Physical Activity Levels

During the ~48-hour experimental situations, diet prescription will follow American Diabetes Association recommendations [49,50] to ensure a personalized diet based on their estimated energy requirements. Meals and snacks will be provided in individualized, pre-weighted packages and will be composed of ~55% carbohydrate, ~15% protein, and ~30% fat. The timing of ingestion will be strictly controlled to ensure a standardized diet. Diet prescription will be done by a registered dietitian nutritionist. The diet will be designed to meet the energy requirements as calculated with the Cunningham equation [51] multiplied by a physical activity level of 1.2 [11].

Participants will be instructed to maintain their habitual physical activity levels, and to not perform moderate- to high-intensity physical activity 72 hours before and during the experimental sessions. Physical activity levels will be assessed using a commercially available accelerometer (GT3X, ActiGraph).

### Statistical Analysis

The sample size was calculated using data from relevant literature using similar individuals and glucose-assessing tools (CGM) [11,14,52,53]. Conservative parameters were inserted in the G*Power program (Heinrich-Heine-Universität Düsseldorf, version 3.1.9.6) for a repeated measure ANOVA within interaction: effect size of 0.2 (for 24-hour average glucose concentrations), probability of error type **α** of 0.05, power (probability of error type 1 β) of 0.95, correlation among repeated measurements of 0.7 [54], and nonsphericity correction of 0.5 [55,56]. With these parameters, 15 individuals are required (actual power of 0.96). Considering a typical dropout rate of 25% to 40%, we will initially recruit 25 participants.

A collaborator outside the research team will double-enter data coded for allocation into a computer in separate spreadsheets, allowing the researcher responsible for data analysis to assess the data without access to allocation information. Allocation will only be revealed after statistical analyses are run. In case of doubts about data entry (missing values or values outside the reference range), the researcher responsible for data analysis will contact the collaborator outside the research team responsible for double entry of the data to check accuracy. There will be no interim analysis.

To ensure confidentiality, all study-related information will be securely stored at the study site. All participant information will be kept in locked file cabinets in areas with access controlled by the principal investigator. All laboratory specimens, reports, data collection, process, and administrative forms will be identified by a coded ID number only to maintain participant confidentiality. Records containing names or other personal identifiers, such as locator forms and informed consent forms, will be stored separately from study records identified by code number. No personal information from participants will be released outside the study. Full access to the complete dataset will be restricted to members of the research team.

The statistical analysis will follow the principles of intention-to-treat analysis [57]. Thus, data from participants will be assessed as randomized, regardless of whether they received the randomized treatment, meaning that even if they fail to follow the physical activity and diet instructions, or fail to complete the sessions as required, their data will be included in the analyses. Furthermore, we will also analyze the data “per protocol” [58], meaning that participants who deviate from instructions will be excluded from the final analyses. Differences in results stemming from intention-to-treat and per-protocol analyses will be discussed accordingly. The available variables will also be compared between participants who withdraw from the study and those who complete the study.

The effect of resistance exercise on glycemic control will be calculated as the absolute and percentage change between control and resistance exercise situations. Data will be expressed as mean and SD, with a 95% CI. For the analysis of data normality, we will perform the Shapiro-Wilk test. For normally distributed data, ANOVA will be used with 1 source of variation (experimental condition). If a significant main effect is observed, the post hoc Tukey test will be conducted. For nonnormal data, the Kruskal-Wallis test or Friedman test will be used as appropriate. The effect size will be calculated and interpreted as follows: <0.2=no effect, 0.2-0.49=low effect, 0.5-0.79=medium effect, and >0.8=large effect [59,60]. The significance level is set at 5%. The Prism program (version 10.1.1, GraphPad Software) will be used to generate graphs and analyze results. This trial will be reported following the CONSORT (Consolidated Standards of Reporting Trials) guidelines [61-63].

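### The stated 15 participants with power 0.96 do not fit a three-condition crossover: under the protocol's own parameters 15 completers give power of about 0.36, and 67 would be needed for 0.95

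*Protocol article*

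**What the plan says.** All of the following is in the protocol article, Methods.

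- **Design** (Study Type and Design): a three-arm randomized crossover in which each participant completes a high-effort, a low-effort and a control session.
- **Power model** (Statistical Analysis): G*Power was run "for a repeated measure ANOVA within interaction", with "effect size of 0.2 (for 24-hour average glucose concentrations"), alpha 0.05, "power (probability of error type 1 β) of 0.95", "correlation among repeated measurements of 0.7" and "nonsphericity correction of 0.5". The article calls these inputs conservative. It does not give the number of groups or of repeated measurements.
- **Result** (same paragraph): "With these parameters, 15 individuals are required (actual power of 0.96"). Recruitment is then raised to 25 for dropout of 25% to 40%.
- **Planned test** (Statistical Analysis): for normally distributed data, "ANOVA will be used with 1 source of variation (experimental condition"), followed by Tukey comparisons if the main effect is significant. "The significance level is set at 5" percent.

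**The concern.** The powered variable is a 24-hour mean, which yields one value per session, and the planned test has condition as its only factor. That fixes one group and three measurements. A standardized effect of 0.2 is small, and 15 people measured three times looked too few to detect it with 0.96 power, even at a correlation of 0.7. The power model is also named as an interaction, whereas the analysis contains no second factor with which condition could interact.

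The consequence lies in how the result will be read. The Introduction hypothesizes that effort will not affect glycaemic control, and the Discussion anticipates similar improvement at both effort levels. A non-significant glycaemic result is therefore close to what the authors expect. A stated power of 0.96 would lend it weight that the trial cannot supply.

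**Working it through.** **Inputs.** From the sample-size paragraph: f = 0.2 (read as Cohen's f, the effect size this procedure takes), alpha = 0.05, target power 0.95, rho = 0.7, epsilon = 0.5, N = 15. From the design and the planned ANOVA: k = 1 group, m = 3 measurements.

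**Formula** (G*Power default for repeated-measures ANOVA):

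- noncentrality: lambda = N × m × f² × epsilon / (1 − rho)
- within factor: df1 = (m − 1) × epsilon; df2 = (N − k)(m − 1) × epsilon
- within-between interaction: df1 = (k − 1)(m − 1) × epsilon; df2 as above

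**Step 1: can the published figure be reproduced?** Only with values of k and m that the article does not state. A search for N = 15 with power rounding to 0.96 found:

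| Model | k | m | Power at N = 15 |
|---|---|---|---|
| Within factor | 1 | 30 | 0.956 |
| Within factor | 1 | 31 | 0.961 |
| Interaction | 3 | 48 | 0.956 |
| Interaction | 3 | 51 | 0.965 |

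For the interaction with k = 3 and m = 48: lambda = 15 × 48 × 0.04 × 0.5 / 0.3 = 48, df1 = 2 × 47 × 0.5 = 47, df2 = 12 × 47 × 0.5 = 282, power 0.956. This would treat the three crossover conditions as three separate groups of five and test group by time. Which inputs were actually used is not documented.

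**Step 2: the planned design and test.** With k = 1 and m = 3:

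- lambda = 15 × 3 × 0.04 × 0.5 / 0.3 = 0.9 / 0.3 = 3.0
- df1 = 2 × 0.5 = 1; df2 = 14 × 2 × 0.5 = 14; critical F = 4.60
- power = 0.365

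At N = 67: lambda = 67 × 3 × 0.04 × 0.5 / 0.3 = 13.4 on F(1, 66), power 0.950. At N = 66 power is 0.947, so 67 is the minimum.

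**Step 3: sensitivity to sphericity.** For three conditions, 0.5 is the lowest value epsilon can take, 1/(m − 1).

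| Epsilon | Power, N = 15 | Power, N = 25 (no dropout) | N for 0.95 |
|---|---|---|---|
| 0.5 | 0.36 | 0.57 | 67 |
| 0.75 | 0.46 | 0.70 | 50 |
| 1.0 | 0.54 | 0.79 | 41 |

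A simulation at N = 15, with f = 0.2 and all pairwise correlations 0.7, rejected in 0.537 of trials with the uncorrected test and 0.373 with lower-bound degrees of freedom. This agrees with the formula.

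**Step 4: what 15 completers can detect.** Power 0.95 at m = 3 needs f = 0.45 (epsilon 0.5) or f = 0.34 (epsilon 1).

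**Step 5: precision of high minus low.** In units of the between-person SD, the standard error is √(2 × (1 − 0.7) / 15) = 0.20. The 95% half-width is 0.41 SD with the pooled error (28 df), 0.43 SD as a paired interval (14 df), and 0.49 SD with Tukey adjustment.

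**Step 6: dropout.** 15 / (1 − 0.40) = 25. The inflation is right; the fault is in the base figure of 15.

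**The case against.** The strongest reply is that two required inputs, the number of groups and of measurements, are not given. On that view the stated parameters alone fix no answer, and 15 with 0.96 may be a valid program output for some other model. That is probably so, and a condensed article may leave such inputs to a fuller document. It does not help the claim. The design and the planned ANOVA supply the missing values, and the models that return 15 with 0.96 test something the analysis does not contain. Even counting six values per person (three sessions, two 24-hour periods) gives power of only 0.50.

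A second reply is that 0.2 might mean f². Then f = 0.447, power at N = 15 is 0.949 and 16 participants are required. That is close, but it is not the stated result, and f² is not what the procedure takes.

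Third, epsilon 0.5 is a floor, so 0.36 is the pessimistic end. This stands, and the range 0.36 to 0.54 should be quoted. The favourable end is still far from 0.96.

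Fourth, 0.36 is the power of the three-condition omnibus test, control included, and not of high versus low. This also stands. No passage says a null result will be presented as evidence from a 96%-powered trial, so the misreading is a risk and not a stated intention.

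**Conclusion.** The statement is wrong as written. For the design and test that the protocol describes, 15 completers give the omnibus test power of 0.36 to 0.54, and 41 to 67 completers are needed for 0.95; the protocol's own epsilon of 0.5 gives 0.36 and 67. The planned test would miss the planned effect in roughly 46% to 64% of trials, against the 4% implied. These figures assume f = 0.2 on Cohen's scale, correlation 0.7, alpha 0.05 and G*Power's default effect-size convention. That the stated figure does not fit the design is certain; how it arose is inference.

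**What to change.** Replace the sample-size result with a calculation for one group and three measurements that names both inputs, and remove the 0.96. A suitable statement: with 15 completers, correlation 0.7 and f = 0.2, the omnibus test has power of about 36% (epsilon 0.5) to 54% (epsilon 1); power of 95% is reached only for f of about 0.45 or 0.34 respectively.

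Add the expected 95% half-width for high minus low in the form that will be reported: about 0.43 SD for a paired interval, or 0.49 SD with the planned Tukey adjustment.

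The simplest course is to keep the sample size and present the trial as one that estimates differences with that precision. Raising the sample size, or justifying a larger target effect, would also bring the claim and the design into line; that choice is the sponsor's.

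The cost is revised protocol and analysis-plan wording and a registry update, with a less favourable stated power. Restating the claim needs no extra participants.
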